### Sample size

The study is embedded in a closed longitudinal cohort that has been followed for over 50 years. Consequently, the expected sample size is determined by cohort availability and participants’ willingness to take part at the time of data collection, rather than by recruitment targets. The data collection phase of the 8th wave took place between 2006 and 2009. Out of originally 294 mother–child pairs, 211 participants took part (71% retention rate after almost 40 years). Given the long follow-up interval, expected age-related attrition, and loss to follow-up typical of long-term cohort studies, a reduction in participation is anticipated. In addition, the current wave includes assessments related to COVID-19–related experiences, which represent a potentially sensitive topic and may further affect participation rates. Based on these considerations and prior participation patterns, we expect to recruit approximately 150 participants in the current wave (~50% retention rate after 55 years). All eligible participants will be systematically contacted and invited to participate using repeated and respectful procedures. At the beginning of recruitment in February 2022, participants were around 52 years old. Data collection started in April 2022. At the time of submission of the study protocol, data of 103 individuals have been collected. We expect a subsample size of 50% for blood sampling and imaging procedures as they are unfamiliar to our participants and may be met with hesitation.

### Constructs

Measures consist of extensive online questionnaire packages, a semi-structured face-to-face (F2F) interview including mapping the social network (via the “Network Canvas”-app), blood sampling for genetic analysis, functional magnetic resonance imaging (fMRI), ecological momentary assessment (EMA) using smartphones, and an online follow-up survey 14 days post interview. The assessment battery was harmonised across the three cohorts and not all collected measures are analysed in the present manuscript. An in-depth description of all measures can be found in the Supplementary material.

### Recruitment and participant timeline

Participants are sent an invitation letter and detailed information about the 9th wave of the ROLS by mail and asked to send back their signed informed consent prior to providing any study data. Additional consent forms are included for optional study parts (blood sample, fMRI), and upon return, screened for potential contraindication (e.g., pacemaker). Non-responsive participants are then contacted by phone, in case of a valid phone number, receive reminder letters or are visited at home by a member of the team to see if their address is still correct. As Germany does not have a central registry for its citizens, identifying the participants’ whereabouts is a time- und resource-consuming task. As participants have indicated their consent to be contacted for future surveys during previous waves, inquiries are sent to the local registry’s office to update personal data such as last name and/or address.

Participants are provided with individualised access to online questionnaires 4 weeks before the F2F interview. Completion of the questionnaire is estimated to take approximately 2 h. To reduce participant burden and fatigue, the questionnaires are divided into six sections, each requiring approximately 20 min to complete (“Alltag und Psyche”-Daily life and psyche, “Gesundheit”-health, “Stress und Stärken”-stress and strengths, “Zur Person 1”-about the person 1, “Zur Person 2”-about the person 2, “Corona und Netzwerk”-corona and network). Participants are allowed to complete the questionnaire in multiple sessions. Progress is saved automatically, allowing participants to pause and resume completion without loss of previously entered data. To ensure data completeness and standardisation, all items within each section require a response before participants can proceed. To minimise missing data and participant attrition, completion of the online questionnaires is monitored by the research team. In cases where one or more sections remain incomplete, participants will receive reminders via email and, if necessary, follow-up contact by telephone. The semi-structured interview, lasting between two and 3 h, is conducted in person in accordance with the prevailing local regulations pertaining to the COVID-19 virus until such time as they were rescinded by the German government in March 2023. For participants who can or will not come to the clinic, home visits are rendered possible throughout Germany and neighbouring countries. The mapping of the social network is collected via the “Network Canvas Interviewer”-app which is installed on Android-based study tablets. The neurobehavioural battery is performed during the F2F appointment, either using a laptop in case of home visits or using functional magnetic resonance imaging in cooperation with the Centre for Diagnostic and Interventional Radiology (ZfDIR) at the University Medical Centre Rostock. An optional ecological momentary assessment (EMA) of 14 days following the F2F meeting is employed, completed by a 5-min, follow-up online questionnaire about the participant’s experiences with the smartphone assessment as well as additional scales. Participants receive an expense allowance depending on their participation amounting up to 150€ (questionnaires and F2F interview–50€, fMRI–50€, EMA–50€).

### Recruitment and sampling procedure

Research assistants are trained to promote quality assurance and will attend regular meetings to explore any difficulties encountered. The training encompasses an explanation of the rationale behind the study, how to take informed consent, how to administer online questionnaires, how to conduct the semi-structured interview and observations in a standardised procedure. Blood samples are taken and fMRI is conducted by trained medical staff of the clinic in cooperation with radiological technologists. Any unexpected, adverse events encountered during F2F-meetings will be reported and assessed within the study team.

### Plans for assessment and collection of outcomes

Participants who have given their informed consent are contacted individually by phone to arrange an appointment for the F2F meeting. Applying a two-stage process, participants receive an e-mail containing links to the online questionnaires, which are to be filled in before meeting with a researcher in person. Preliminary analyses of questionnaire data are used to feed the semi-structured interview. Interviews are not recorded but instead notes are taken by the research assistant. As part of this F2F interview, the social network will be mapped, the blood sample is taken, and the neurobehavioural battery is conducted.

### Data management

Personal information on potential and enrolled participants are maintained in order to protect confidentiality by replacing personal data with a pseudonym throughout the study and its use within the consortium. Electronic data such as online questionnaires, fMRI, and social network data will be stored on servers of the University Medical Centre Rostock, with only the research team having access to study and personal data. Paper-and-pencil data will be stored in the ROLS archive in fireproof lockers. Blood samples are being stored at a lab specialised in biological research data (Biobank Psychischer Erkrankungen, Zentralinstitut für Seelische Erkrankungen, Mannheim, Germany).

### Plans for collection, laboratory evaluation, and storage of biological specimens for genetic analysis in this trial

Pseudonymised blood samples for genetic analysis are stored at a cooperating institute at the Central Institute of Mental Health in Mannheim. DNA will be extracted and examined for the existence of risk genes of substance use using genome-wide association studies. Participants indicate their consent for future use in ancillary studies; if not their blood sample is destroyed after the current investigation. The fMRI data are not screened by radiologists but participants have access to their data on request. On completion of the study, the data will be analysed and a final study report will be written. Participants will be notified of any publications if they have expressed an interest. Participants have the opportunity to review all their data and the right to have their data deleted and blood sample destroyed.

### Data analysis

Data will be analysed in two ways simultaneously. First, ROLS data will be entered into combined analyses of all consortional data. The foundations for this comparative work have been laid, including the development of tools for harmonising all three data sets, notably a Natural Language Processing-based semantic search approach using embedding models to identify semantically similar questionnaire items across heterogeneous instruments, thereby reducing manual effort and supporting valid cross-study harmonisation (70).

Second, ROLS data will be analysed within the study’s framework. Analyses of this kind are limited by the sample size, however, they will benefit from the long period analysed prospectively, the number of measurements, and the richness of the data. Letter points will allow for effective imputation methods, since certain constructs were investigated on multiple occasions. In the context of secondary data analysis, the basic principle is to “make the best of what you have” (71), meaning, that—to certain extent—methodologies must be adapted to the specific characteristics of the data being analysed.

Data of the 9th wave will be analysed once participants have completed all study parts and no interim analysis will be performed. The data collection process will be terminated, when all participants expressing interest in participation are met in person. As for the analysis of the hypotheses mentioned above, methods will be the following: (1) Coping profiles and their trajectory across adulthood will be analysed using latent profile transition analysis implemented as a hidden Markov model. Habitual coping, assessed consistently with the Stress Management Questionnaire (72) at three time points (6th, 8th, and 9th waves), will be used to identify qualitatively distinct profiles and probabilistic transitions over three decades, whilst accounting for measurement error. This person-centred approach is appropriate considering the theoretical interest in stable and changing patterns of coping rather than continuous change in individual strategies. Given three waves over decades, we will use Full Information Maximum Likelihood (FIML) to handle missing data. Post-hoc profiling of coping trajectories and their associations with health and well-being in late middle age will include analyses of variance and appropriate non-parametric alternatives. (2) The role of lifelong coping profiles during the COVID-19 pandemic will be investigated using linear mixed-effects models (LMMs) with monthly psychosocial strain ratings (on a Likert-type scale ranging from 1 to 5) over 3 years of the pandemic (March 2020 to March 2023) as the outcome. To address potential memory bias during retrospective data collection, participants are given brief descriptions of currently valid COVID-19 restrictions for each month. Coping profile membership will be included as a fixed effect, with piecewise time segments representing stricter versus less restrictive pandemic periods. Random intercepts and random slopes for time will model baseline differences and individual variation in trajectories. To account for varying recall periods between the month being rated and survey completion, recall delay (in weeks) will be included as a covariate in all LMMs. Interactions between coping profiles and piecewise time will test whether certain profiles buffer or exacerbate psychosocial strain. (3) Alcohol use to cope trajectories from emerging adulthood to late middle age will be analysed using latent growth mixture modelling on the alcohol-related items of the subscale substance use to cope (Stress Management Questionnaire) for three time points (6th, 8th, and 9th waves), missing data will be handled using FIML. Trajectory membership will be used to predict alcohol consumption during the COVID-19 pandemic by fitting linear regression models, and potential sex effects will be explored using the three step approach with multinomial logistic regression models. Whilst the identification of coping and alcohol-use trajectories across adulthood is primarily exploratory given the uniqueness of the cohort and the absence of comparable long-term studies (Objectives 1–3), the investigation of neurobehavioural and social influences on coping during the COVID-19 pandemic (Objectives 4–6) is theory-guided and builds on prior evidence regarding stress regulation, executive control, reward processing, and social integration. (4) Functional MRI data will be analysed using standard pipelines in SPM, running in MATLAB, including standard preprocessing. For task-based fMRI, individual-level contrasts for the onset of event types will be modelled and general linear models (GLMs) will be specified for the Stop Signal Task (Go, Successful Stop, Failed Stop) and Monetary Incentive Delay task (cue, anticipation, outcome), with regressors convolved with the canonical hemodynamic response function. At the group level, we will extract activation measures from regions of interest, including ventromedial prefrontal cortex (vmPFC) for cognitive control and mesostriatal regions for reward anticipation that will first be examined as predictors of longitudinal psychopathological strain during the COVID-19 pandemic using linear mixed-effects models (LMMs). Monthly strain ratings will serve as the outcome, with ventromedial prefrontal cortex activation (Stop Signal Task) and mesostriatal reward anticipation (Monetary Incentive Delay task) included as time-invariant predictors. Piecewise time segments representing periods of stricter versus less restrictive measures will be specified, along with random intercepts and random slopes for time, to model individual differences in baseline strain and trajectories. Interactions between neural activation and time will be tested to assess buffering or vulnerability effects across pandemic phases. In a second step, self-reported control strategies as assessed with the Optimisation in Primary and Secondary Control Scale (73) during the pandemic will be examined as potential mediators of the association between neural activation and psychopathological strain. Mediation analyses will be conducted using multilevel mediation models, with neural activation predicting control strategies and control strategies predicting longitudinal strain, whilst accounting for the repeated-measures structure of the outcome. Indirect effects will be estimated using appropriate methods for multilevel data (e.g., Monte Carlo or bootstrapped confidence intervals), allowing evaluation of whether neurobehavioural markers influence pandemic-related strain through engagement in specific coping strategies. MPRAGE, resting state, and DTI data will be analysed by the consortium later on. (5) Social network analysis will consist of an examination of key egocentric metrics—including network size, density, degree centrality, and constraint—that will be calculated and visualised using R with the *igraph* and *egor* packages, or Network Canvas’s built-in analytics. Alter-level data on vaccination behaviour, adherence to COVID-19 restrictions, and health behaviours relevant to coping (e.g., physical activity, alcohol consumption) will be used to characterise the behavioural composition of each ego network. In a second step, Exponential Random Graph Models (ERGMs) for small networks (*ergmito*) (74) will be fitted to investigate homophily in vaccination and clustering in preventive and health-related behaviour during the COVID-19 pandemic, using exact statistical calculations instead of simulation-based approximations. Separate models will be specified for vaccination and restriction adherence as well as for health behaviours conceptualised as coping efforts (e.g., exercise, alcohol use). These analyses will test whether similarity in health-related coping behaviours is greater than expected by chance and whether socially embedded behavioural patterns contribute to adaptive or maladaptive coping during a health crisis. (6) For the accentuation hypothesis, several ways will be tested to verify it. First, deviations in panel samples should increase for several outcomes, such as alcohol consumption or positive health behaviour. If deviations increase within the health behaviour data, the hypothesis should be tested that persons remain stable with regard to their ranks in outcomes before and during or after the crisis. In a third approach, individual changes in different outcome measures should be analysed for their direction and magnitude. Changes towards the edges of distributions will speak for the accentuation hypothesis, changes towards the centre for a regression to the mean. Changes of both kinds will then be modelled as the dependent variable in several regression models including coping trajectories mentioned above and predictors from various domains, such as social relations, COVID-associated burdens, brain associated mechanisms or genetic risks (PRS). Analyses were restricted to measures relevant to the predefined research questions of the ROLS and other harmonised measures are reserved for future consortium analyses.

Together, these analyses integrate developmental coping profiles, neurobehavioural markers, and egocentric social network characteristics to identify individual and social determinants of health behaviours and psychosocial strain during the COVID-19 pandemic, informing public health strategies for promoting adaptive coping and preventive behaviour in future health crises. As this study represents a long-term, evolving cohort project, additional opportunities for exploratory analyses may arise as new questions, methods, and standards emerge. These investigations will be clearly distinguished from the pre-specified, theory-driven objectives (Objectives 4–6) and the primary exploratory objectives (Objectives 1–3), and will be undertaken as hypothesis-generating analyses when scientifically justified, for example using emerging methods such as machine learning.

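### Recall delay is reversed calendar time within a person: it shifts and widens the main pandemic slopes but not the interaction tests, whose error rate depends on which time slopes are random

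*Protocol article*

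**What the plan says.** Data analysis, item (2), models strain scored once per month on a 1-to-5 scale, "over 3 years of the pandemic (March 2020 to March 2023) as the outcome". The time and group terms are these: "Coping profile membership will be included as a fixed effect, with piecewise time segments representing stricter versus less restrictive pandemic periods". On the random part: "Random intercepts and random slopes for time will model baseline differences and individual variation in trajectories". On recall: "recall delay (in weeks) will be included as a covariate in all LMMs", where delay is the time from the rated month to the date the person completed the survey. The question is answered by interactions: "Interactions between coping profiles and piecewise time will test whether certain profiles buffer or exacerbate psychosocial strain".

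Item (4) uses the same outcome, the same time segments and the same random terms, with brain activation in place of profile: "Interactions between neural activation and time will be tested to assess buffering or vulnerability effects across pandemic phases".

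The Sample size section adds that "Data collection started in April 2022" and that recruitment was still under way at submission (103 of about 150 expected), so survey date differs between people. The text does not say whether the segments are level steps or connected slopes, whether there is one random slope or one per segment, or how residuals within a person are correlated.

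**The concern.** Two separate things look wrong.

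First, delay is meant to remove the effect of fading memory. By its definition it carries no within-person information beyond the calendar month itself. Its coefficient must then come from comparing people surveyed early with people surveyed late. These may differ for other reasons: the recruitment section describes calls, reminder letters and home visits for non-responders, and local COVID-19 rules ended in March 2023 while collection was running. Any such difference would be carried into the reported pandemic slopes.

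Second, the tests of interest are interactions with period. If the model lets people vary only in level and in one overall linear trend, differences in how strongly people react to strict periods have nowhere to go except the residual. So does correlation among up to 37 ratings recalled in one sitting. Standard errors for the interactions would then be too small, and a buffering or vulnerability effect could be declared by chance.

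**Working it through.** The protocol gives no alpha, variance, effect size or power for these models, so there is no figure to reproduce.

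**Inputs from the protocol:** delay = survey completion date minus rated month; window March 2020 to March 2023, which is 10 + 12 + 12 + 3 = 37 months; about 150 participants, about half of them imaged; collection from April 2022.

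**Assumptions:** three profiles of 50; six segments in the piecewise-linear case; survey dates spread over 12, 24 or 36 months; intercept SD 0.6, linear slope SD 0.25 per year, residual SD 0.7.

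**1. Algebra.** With S_i the survey date and t the month, delay = S_i − t, so

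b·t + c·(S_i − t) = (b − c)·t + c·S_i.

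The data fix (b − c) within people and c only between people, through S_i. The printed slope is b = observed slope + c. With piecewise-linear time the segments sum to t, so the same holds for each segment. The within-person design has rank 7 (intercept plus six segments) with or without delay.

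**2. Shift.** With no true trend, no recall effect and a survey-date difference of 0.1 points per year, fitting delay gave main slopes of 0.1 per year in all six segments instead of 0.

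**3. Precision.** Since b = observed slope + c, Var(b) ≈ Var(observed slope) + Var(c). For the last segment, whose SE without delay is 0.099:

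| Survey spread | SE of c per year | √(0.099² + SE²) | Computed SE |
|---|---|---|---|
| 12 months | 0.1741 | 0.200 | 0.200 |
| 24 months | 0.0865 | 0.131 | 0.132 |
| 36 months | 0.0573 | 0.114 | 0.115 |

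At 36 months the SE ratio is about 1.11 to 1.17 with six segments and about 2.1 with two, so the widening depends on a layout the protocol does not give.

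**4. Interactions.** One coefficient c applies to all profiles, so it cancels from differences between them. Interaction estimates were identical with and without delay and their SE ratio was 1.000, also when months after the survey date were dropped. For the same reason, delay does not correct recall effects that differ by profile.

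**5. Step-coded periods.** Delay is no longer aliased (within-person rank 2 becomes 3), but it acts as a linear trend. With a true trend of −0.2 per year, a true period effect of 0.30 and no recall effect, the period estimate was 0.457 without delay and 0.384 with it. The delay coefficient was 0.093 per year although no recall effect existed. The interaction stayed at 0.20.

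**6. Interaction tests with one linear random slope and independent residuals.** Suppose people differ in their period effect with SD 0.3. The difference between two profiles of 50 then carries extra chance variance of 2 × 0.3² / 50 = 0.0036 (SD 0.06 points), which this model has no term for. Rejection rates of the Wald test at nominal 5%, 400 data sets per setting:

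| Setting | Step coding | Piecewise-linear |
|---|---|---|
| No extra heterogeneity, no serial correlation | 5.3% | 5.0% |
| Period-effect SD 0.2 | 14.0% | – |
| Period-effect or segment-slope SD 0.3 | 23.8% | 9.0% |
| Period-effect or segment-slope SD 0.5 | 46.5% | 11.0% |
| SD 0.3, ratings rounded to 1–5 | 21.3% | – |
| AR(1) 0.5 alone | 23.3% | 63.8% |
| SD 0.3 and AR(1) 0.5 | 39.3% | – |

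The Monte Carlo SE near 5% is √(0.05 × 0.95 / 400) = 1.1 points. A second simulation gave about 20% with SD 0.3, 15% to 48% with AR(1) 0.5 depending on time coding, and 3% to 7% with neither.

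**7. After the fix.** With a person-level random effect on the period term (step coding), SD 0.3 gave 6.8% with independent residuals and 4.3% with AR(1) 0.5. Person-clustered variance brought the rates in the second simulation to about 3% to 8%.

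**8. Window.** A participant completing in April 2022 has not lived through May 2022 to March 2023: 8 + 3 = 11 of the 37 months.

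**The case against.** The strongest reply is that the delay term does not touch the hypotheses. Objectives 2 and 4 concern profiles and neural markers, and these are tested by interactions, which step 4 shows are unchanged. This stands. A reader might infer that delay biases the buffering tests; it does not.

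Second, the shift in the main slopes is the intended correction if recall acts linearly and survey date is otherwise unrelated to strain. This also stands as a condition. The protocol describes extra contact for non-responders but nowhere says that late participants report more strain, so bias is possible, not shown.

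Third, putting survey date in place of delay is the same fitted model under piecewise-linear time. That is correct; survey date alone changes only which slope is printed. The added survey date × time term is what makes the difference.

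Fourth, the plural random slopes follow directly on a sentence that defines time as segments, so one slope per segment may already be meant, and residual structure is often left to a fuller plan. It is therefore tempting, but not supported, to say that the stated model is anti-conservative. It is so only under the single-slope reading with independent residuals, and then only if reactivity differs or ratings are serially correlated.

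Fifth, nothing says that participants rate months still to come or that such months will be imputed. A mixed model accepts unequal numbers of months, so this is a minor point of wording. Finally, item (2) is labelled exploratory, though item (4) is theory-driven and shares the same model.

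**Conclusion.** The point holds in a limited form. By the protocol's own definition, delay is aliased with calendar time within a person when time is piecewise-linear. It moves all main calendar slopes by one between-person coefficient and makes them less precise; with step-coded periods it absorbs linear trend. It is a source of bias only if early and late participants differ in strain or recall is not linear, and the interaction tests are neither shifted nor protected.

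The interaction tests carry a separate, conditional risk. Under one linear random slope with independent residuals, rejection at nominal 5% was roughly 15% to 50% in most settings tried, with 9% and 64% at the extremes, and about 5% when neither heterogeneity nor serial correlation was present. All these sizes rest on assumed variances, phase layout and survey spread, and item (4), with about half the sample, was not simulated separately. The direction is firm; the amount is not. This is a cheap improvement to the plan, not an error that must be corrected before the study can be interpreted.

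**What to change.** - State whether the segments are steps or connected slopes.
- Replace month-level delay by the person's centred survey date plus survey date × time. The main slopes then read as slopes of recalled strain, and the interaction tests whether recalled trajectories change with lag. For example, a quadratic recall effect c·(S_i − t)² contains −2c·S_i·t. A strictly linear recall effect still cannot be told apart from a survey-date difference, and the text should say so.
- Give each segment term that is interacted with profile or activation a person-level random effect, and use AR(1) residuals or person-clustered robust standard errors.
- Treat months after a person's completion date as structurally missing and do not impute them.

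The cost is a few sentences, a few more parameters and wider intervals for the interactions. No new data are needed. The protocol plans no interim analysis and analyses wave-9 data only after participants have completed all parts, so the wording can be settled beforehand.
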